
#### Other variables

At each outcome assessment point, we will ask participants whether they have started any other treatment for pain or depression during the study, as concurrent therapies are not allowed. Furthermore, information about health behaviors and activities, such as tobacco or marihuana smoking, alcohol consumption, exercising, and participation in recreational activities, will also be recorded.

#### Patient’s treatment satisfaction

After completing the intervention participant’s treatment satisfaction will be assessed using the Client Satisfaction Questionnaire-8 (CSQ-8) [36]. This instrument is comprised of eight items. Its scores range from 1 to 32. Its Spanish version has adequate psychometric properties [37]. In addition, a modified version of the Verona Service Satisfaction Scale (VSSS) [38], comprising 14 items assessing satisfaction with the therapists and other aspects of treatment will be administered.

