## Methods

### Overview of the study design

The present study is a randomized clinical superiority trial with a parallel design. Women with fibromyalgia and major depression will be randomized to either of two intervention arms: an experimental arm – that will be treated with BA in a group setting in addition to UC – and a comparison arm that will continue receiving only its UC. The comparison between these two groups will allow us to establish the potential benefits of adding group BA to the patient’s UC. Outcomes will be assessed in both groups before, during, and after the intervention, as well as after a 3-month follow-up, by a research assistant who will be blind to group assignment. The schedule of enrollment, interventions, and assessment is presented in Fig. 1 (see also Additional file 1: Standard Protocol Items: Recommendations for Interventional Trails (SPIRIT) Checklist).

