### Randomization

Participants who meet all the inclusion criteria after the eligibility interview will be randomized to the two arms, with a 1:1 allocation ratio. We plan to randomize every time we are able to recruit enough participants for a treatment group and a control group. That is, randomization will take place with 16 participants each time, eight of them being assigned to the experimental arm and the other eight to the control. Nonetheless, due to recruitment and logistics issues, it is possible that sometimes a smaller or bigger group of participants needs to be randomized into the two arms. Randomization will be conducted by an independent researcher (not involved in the assessments, treatment, or data analysis). The project coordinator will submit an email to this independent researcher with the ID numbers of participants to be randomized. This researcher will use a computer program to randomly assign participants to the control and the experimental groups. The researcher will then submit a pdf file to the research coordinator with the assignment and will keep a copy for record. The project coordinator will be the only person from the team who is aware of participant allocation, and will keep this information in a file in her computer protected with a password. The principal investigator, co-investigators, and statistician will be blind to participant allocation. The project coordinator will then contact participants to inform them about the initiation of treatment. Notably, all participants will receive the BA intervention at some point. The only difference between the experimental and control groups will be that the former will receive treatment before participants in the control group. To minimize bias, all participants will be informed that they will wait before receiving the intervention and that they will be assessed periodically until their treatment begins, but they will not be aware of how long they or the other people in the study will have to wait. They will also be informed that nobody will wait more than 6 months.

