## Data collection

Outcome data will be collected using standardized questionnaires, that will be administered by telephone as a structured interview by several research assistants. Outcome assessment will take place at four time points in both arms: (1) at baseline, (2) when the experimental arm is under treatment (between sessions 6 and 7), (3) immediately after the experimental arm complete the treatment, and (4) at a 3-month follow-up. As such, participants will be assessed during 5 months. Participants who drop out from the intervention will still be contacted for follow-up assessments. Research assistants will be blind to the aims and hypotheses of the study. As a compensation, patients will receive a gift card (with a value of 10,000 Chilean pesos) after each outcome assessment interview.

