There are some limitations to the study design. First, all the instruments employed are self-report scales. Second, the follow-up assessment will take place at 3 months and studies with longer follow-up must be conducted in order to know whether the effects of the treatment are maintained in the long term. Third, participants under treatment with an antidepressant other than duloxetine will be excluded and, therefore, our results may not generalize to these participants. Nonetheless, requiring all subjects to be receiving duloxetine makes the sample more homogeneous, which is important in randomized clinical trials. Furthermore, as all participants will present with depression despite being under treatment with duloxetine, they will be considered unresponsive to duloxetine treatment. Thus, if we find that adding BA to UC reduces depressive symptoms, this can be interpreted as evidence that BA may be useful for patients who are refractory to duloxetine treatment. Finally, complete blinding of subjects is impossible given the type of intervention and fibromyalgia. Nevertheless, in this study all participants will receive the BA intervention at some point. The experimental and control groups will only differ in that the former will receive treatment before participants in the control group. As such, all participants will know that they will have to wait to receive the intervention, but they will not be given precise information about how long they will have to wait to receive it. Thus, they will not be aware of whether they are in the experimental group or in the control group. Finally, patients are known to be susceptible to placebo effect regarding pain [42], so future studies in which the effect of adding BA to UC is compared with the effect of adding an active intervention for depression to UC are still needed.

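### Participants are said not to know their arm, but only one arm attends sessions before the self-reported primary outcome, and the comparator is usual care while waiting for BA

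*Protocol article*

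**What the plan says.** **Participants.** The Randomization section explains that everyone is told she will wait, is not told for how long, and will be assessed from time to time until her treatment starts. It adds: "Notably, all participants will receive the BA intervention at some point". The Discussion first concedes that "complete blinding of subjects is impossible given the type of intervention and fibromyalgia", then relies on the undisclosed wait to conclude: "Thus, they will not be aware of whether they are in the experimental group or in the control group".

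**Assessors.** The Overview of the study design says that outcomes are assessed "by a research assistant who will be blind to group assignment". The Data collection section says that several assistants conduct structured telephone interviews, and adds: "Research assistants will be blind to the aims and hypotheses of the study".

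**Comparator.** The Abstract (Methods) and the Overview describe the comparison arm as receiving UC only. The Randomization section and the Discussion say that this arm receives BA later.

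**Items that touch on treatment.** Under Other variables: "At each outcome assessment point, we will ask participants whether they have started any other treatment for pain or depression during the study". Under Patient's treatment satisfaction, the CSQ-8 and a modified VSSS are given after the intervention, the latter "comprising 14 items assessing satisfaction with the therapists and other aspects of treatment will be administered".

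**The concern.** The PHQ-9 is the participant's own report. If she knows whether she has been treated, the measurement is unmasked, whoever asks the questions. Women who have just finished a course of group therapy may report improvement partly because they expect it. Women who know they are still waiting may report less. Both tendencies would favour BA.

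A reader who accepts that participants were unaware of their arm would give the result more weight than the design can bear. The comparator label adds to this. The Overview says the comparison will establish the benefit of adding group BA to UC, but the control condition includes knowing that BA is promised and has not begun. The trial cannot separate the effect of BA from the effect of being left to wait.

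**Working it through.** The article gives no figure on this point, so the main check sets its statements against one another.

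1. *Who gets BA in the comparison period?* Experimental arm: 10 group sessions over 2 months, added to UC (Experimental arm section). Control arm: duloxetine and other UC continue, with no sessions (Control arm section).
2. *When is the outcome taken?* At baseline, between sessions 6 and 7, immediately after the experimental arm finishes, and at 3 months (Data collection). The primary outcome is PHQ-9 severity at the end of treatment (Primary outcome).
3. *Who supplies it?* The participant, by telephone. The Discussion lists self-report as a limitation of all the instruments.
4. *What does each woman know by then?* By the second assessment an experimental-arm woman has had six sessions, and by the third all ten have been held. A control woman has been offered none and knows that she is waiting.
5. *What does the undisclosed wait achieve?* Before sessions start, neither group can tell who will be called first, so allocation is masked at baseline. Once one group is called, that protection ends. All three later assessments, including the primary one, fall after that point.
6. *Does the information given to participants fit?* They are told of assessments up to the start of their treatment. Experimental-arm women are assessed during and after it, so for them the description stops matching what happens.

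Steps 1 to 5 contradict the Discussion's conclusion without any assumption about interview procedure.

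**Illustration of what is at stake.** The document gives no size for reporting bias, so the bias is assumed here. Take 45 women per arm, no true effect, two-sided alpha 0.05 (assumed; the article states none), and a reporting bias of b standard deviations on the PHQ-9 in favour of BA. For a simple two-arm comparison, which simplifies the planned hierarchical model:

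P(significant in favour of BA) = Φ(b / √(2/45) − 1.96), with √(2/45) = 0.211.

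| Assumed bias b (SD) | b/0.211 − 1.96 | Probability |
|---|---|---|
| 0 | −1.96 | 2.5% |
| 0.1 | −1.49 | 6.9% |
| 0.2 | −1.01 | 15.6% |
| 0.3 | −0.54 | 29.6% |
| 0.5 | 0.41 | 66.0% |

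The table shows only that a modest bias would matter at this sample size. It is no estimate of the bias in this trial.

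**The case against.** **Lack of participant masking is inherent and partly conceded.** Any trial of a psychological therapy against UC has it. The Discussion says complete blinding cannot be achieved, names self-report as a limitation, mentions susceptibility to placebo effects on pain, and calls for an active comparator in future. All of this stands, and the absence of masking is not itself the fault. The fault is the conclusion drawn in the same paragraph, which the concession does not remove.

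**The sentence may be about the label.** Since everyone eventually receives BA, a woman in sessions might not know whether she counts as experimental. That may be so, but what can colour her answers is knowing that she has had BA or has not, and she does know that.

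**The comparator is not concealed.** The article openly says that controls receive BA later, and UC only is a correct account of the treatment they get during the comparison. That stands too. The correction concerns the label and the scope of the conclusion, not the design.

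**A stronger reading: assessors are unblinded at the primary time point.** A reader might infer this because the satisfaction scales fall under the heading on baseline and follow-up interviews, and because each assessment asks about new treatments. The document does not show it:

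- The opening list under that heading does not name satisfaction. Adherence sits under the same heading, yet consists of attendance records and video recordings.
- Neither the order of questions nor the person giving the scales is stated, and Fig. 1 is not available here. If the PHQ-9 comes first, the primary score is already recorded.
- The treatment question concerns other treatment, because concurrent therapies are not allowed. It may prompt a mention of BA but does not ask about it.
- Blinding to aims and hypotheses is best read as adding to blinding to assignment, not replacing it.

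For the same reasons, it cannot be said that the satisfaction items would reveal the whole experimental arm to the interviewer.

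**Conclusion.** The point holds at participant level. The statement that women will not know their arm is incompatible with one arm attending sessions before the end-of-treatment PHQ-9. The primary outcome is therefore unmasked self-report, for all 90 women and at each of the three assessments after baseline. The contrast is BA plus UC against UC while waiting for promised BA. This rests only on the article's own account of arms, timing and mode of assessment. The likely direction of bias favours BA; its size is unknown.

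At assessor level there is a risk and no more. It is inferred from where the satisfaction scales are placed and from the wording of the concurrent-treatment question. It justifies an inexpensive safeguard, not a finding that blinding fails.

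**What to change.** 1. In the Discussion, withdraw the statement that participants are unaware of their arm. Say instead that the undisclosed wait masks allocation until sessions begin, and that the primary outcome is unmasked self-report.
2. In the Abstract, the Overview and later reports, name the comparator as UC plus waiting list, and limit the conclusion to BA plus UC against that condition.
3. As a safeguard for the assessor blinding claimed in the Overview:
   - ask the PHQ-9 first, then the other outcome scales, and only then the concurrent-treatment and adverse-event questions in the same call, leaving the suicide-risk procedure in Data management as it stands;
   - open each call with a request not to mention sessions or waiting;
   - have the project coordinator, who already knows allocation, collect the CSQ-8 and VSSS after the end-of-treatment outcome interview.

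Items 1 and 2 are changes of wording. Item 3 needs a reordered interview script and some extra coordinator time, with no new staff. It protects the assessor only. Nothing in it masks the participant, so items 1 and 2 are needed in any case.

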#### Adherence

Attendance to treatment sessions will be tracked as a measure of adherence. Treatment sessions will be video recorded and classified according to the phase of treatment (beginning, half, or end of treatment) in order to assess therapist adherence to the clinical guide. A research assistant will randomly select 20% of these sessions, which will be analyzed according to the adherence checklist included in the BA manual by two psychologists trained in BA.

### Data management

Collected paper questionnaires will be kept locked in a cabin within the office of the principal investigator, separated from the signed informed consent documents. To protect confidentiality, the questionnaires will not include personal identification information and they will be linked to each participant by a code randomly created by a computer. A file with the link between participants and their codes will be password-protected and kept in a computer in the office of the principal investigator. A research assistant who will be blind to randomization will enter the information into a password-protected database that will also be kept in a computer in the office of the principal investigator. Another blind research assistant will double check 10% of the data entered for data quality purposes. A data monitoring committee has not been deemed necessary because all participants receive UC and the intervention is not expected to lead to serious adverse events. However, adverse events will be monitored as part of the outcome assessments, including assessment of suicidal ideation. In case of imminent suicide risk, the participant’s physician and a close relative (who will be designated by the participant during the informed consent process) will be contacted and given instructions to take care of the patient, including taking them to an emergency psychiatric unit. If the designated family member is not available at the time, the patient will be taken to an emergency psychiatric unit by a research assistant.

### Analytic plan

#### Data analyses

In order to test whether there are differences between the two groups in the sociodemographic and clinical characteristics assessed at baseline, Student’s *t* tests will be performed for continuous variables and chi-square tests for categorical variables. If there are small or empty cells in the categorical tests, the chi-square test will be replaced by a Fisher’s Exact Test. Those variables in which statistically significant differences are found will be introduced in the analyses as covariates.

In order to examine differences between groups in the reduction of the primary and secondary outcome, HLM will be performed using MPlus. This analysis involves two levels of analysis: within-subject (level 1, which analyzes the change of subjects over time) and between-subject (level 2, through which the effect of treatment is examined). Repeated measures of symptoms are nested in each subject, and the analysis allows for estimating a change parameter along repeated measurements. The analysis tests whether the change parameter varies according to the treatment group, and other covariates. HLM allows one to consider in the analyses all participants (including those who drop out from the study). Therefore, these analyses will be conducted according to the principle of intention to treat. Finally, in order to test whether the decreases found after the follow-up in the pain-related variables are mediated by the decrease in depressive symptom severity, mediation analysis with bootstrapping will be conducted [39].

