#### Sample size calculation

The study sample size was calculated for a Hierarchical Linear Model (HLM) in which the primary outcome (depressive symptom severity) was the dependent variable. Using Mplus [20], we determined that a sample of 90 participants will be needed to reach a power of .80. In this power analysis, the correlation between the intercept and the slope was specified to be − 0.4. The average slope was assumed to be negative, as depression scores are expected to drop, and was specified as − 0.5. To simplify the model, the variances of the intercept, slope, and scores of all the variables in the model (depressive symptom severity, and covariates) were specified as 1, so as to have the standardized model solution. The treatment effect on the slope (standardized Beta) was specified as 0.45. This corresponds to a medium-to-large effect size [21, 22]. In addition, the effect of two covariates was included. The effect of each of the covariates on the slope was specified as 0.1. The correlation between treatment and each covariate was specified as 0.1, and the correlation between covariates was specified as 0.3.

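### Covariates for the primary and secondary models are chosen by significance tests of baseline differences between randomized arms, so chance and not prognostic value decides what is adjusted for.

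*Protocol article*

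**What the plan says.** The protocol article, Analytic plan, Data analyses, begins by testing for "differences between the two groups in the sociodemographic and clinical characteristics assessed at baseline". The tools are Student's t and chi-square ("tests will be performed for continuous variables and chi-square tests for categorical variables"), with Fisher's exact test for sparse tables. No screening level is given. The consequence of a positive test is then set: "Those variables in which statistically significant differences are found will be introduced in the analyses as covariates".

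The next paragraph describes the hierarchical linear model (HLM) for the primary and secondary outcomes and says: "The analysis tests whether the change parameter varies according to the treatment group, and other covariates". The screening rule therefore feeds the primary model. The article names no covariate in advance.

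Two other places bear on this. Under Randomization, eligible participants "will be randomized to the two arms, with a 1:1 allocation ratio", and an independent researcher makes the assignment with a computer program. Under Sample size calculation, the power model allows for covariates without naming them: "In addition, the effect of two covariates was included".

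**The concern.** A covariate earns its place in a randomized comparison by predicting the outcome. A test of baseline difference between arms measures something else: whether this particular randomization happened to split the variable unevenly. Since the null hypothesis of that test is true by design, the rule picks variables at the false-positive rate of the test.

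Three things are at stake. The covariate set of the primary model is not known until the baseline data have been tested. A useful predictor is left out nearly always, and a useless one is as likely to be let in. And the wording does not exempt baseline PHQ-9. If it tested significant, a literal reading would enter it as a covariate while it is also the first repeated outcome.

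**Working it through.** **The plan's own figure.** The article states that "we determined that a sample of 90 participants will be needed to reach a power of .80", with "The treatment effect on the slope (standardized Beta) was specified as 0.45". The significance level, sidedness, time scores and treatment coding are not given. Over plausible choices for these, two-sided power for the growth model ranges from .23 to above .99, so .80 can be neither reproduced nor refuted. The point below does not depend on it.

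**How often a variable enters.** Inputs: 1:1 randomization (article); a 0.05 screening level and k independent candidates (assumed; neither is stated).
- A given variable enters with probability 0.05 and is left out with probability 0.95. Simulation with 45 per arm found a prognostic variable selected in 4.9% to 5.6% of trials.
- At least one enters with probability 1 − 0.95^k: k = 5, 23%; k = 10, 40%; k = 15, 54%; k = 20, 64%; k = 25, 72%.
- The expected number entered is 0.05k, that is 0.25 to 1.25.

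**What it costs in power.** Inputs: 45 per arm (article); d = 0.5, two-sided 5% and all correlations (assumed). A single end-of-treatment comparison adjusted for baseline PHQ-9 stands in for the HLM. The noncentrality is d × √(45/2) / √(1 − R²), where R² is the outcome variance explained by the covariates, and 0.5 × √22.5 = 2.372.
- Baseline PHQ-9 alone, correlation 0.5 with the outcome: R² = 0.25; 2.372/√0.75 = 2.739; power about .77.
- Adding a predictor that correlates 0.3 with the outcome and 0.3 with baseline PHQ-9: R² = (0.25 + 0.09 − 2 × 0.5 × 0.3 × 0.3)/(1 − 0.09) = 0.25/0.91 = 0.275; 2.372/√0.725 = 2.785; power about .79.
- The same with correlation 0.5 with the outcome: R² = (0.25 + 0.25 − 2 × 0.5 × 0.5 × 0.3)/0.91 = 0.35/0.91 = 0.385; 2.372/√0.615 = 3.02; power about .85.

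Simulated trials, which also carry chance imbalance in the covariates, give about .76 with baseline PHQ-9 only, .78 to .84 with one predictor always included, and .74 to .75 under the rule (20 candidates, one of them prognostic).

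**Why the rule can fall slightly below no further adjustment.** A variable that enters is by construction correlated with treatment. At t = 2 on 88 degrees of freedom its squared correlation with treatment is 4/(4 + 88) = 0.043, which multiplies the variance of the treatment estimate by 1/(1 − 0.043) = 1.045. If the variable is not prognostic, nothing offsets this.

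**Type I error.** Under the rule the simulated rate was .045 to .048 with baseline PHQ-9 in the model, and .040 to .049 in a simpler model without it. That is at or slightly below the nominal 5%.

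**The case against.** The strongest reply is that little is lost. Baseline PHQ-9, probably the best predictor, is already in the HLM as a repeated measure, and only what a further variable adds beyond it counts. The article's own planning values are small: an effect of 0.1 on the slope for each of two covariates that correlate 0.3. Together these explain 0.01 + 0.01 + 2 × 0.1 × 0.1 × 0.3 = 2.6% of the slope variance, taken as 1. In the single-endpoint approximation at d = 0.5 that lifts power only from .65 to .66. The rule is also stated in advance and uses baseline data only, so outcome results cannot steer it. All of this stands. It limits the size of the point, but it gives no reason to select on chance imbalance.

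Three stronger readings are tempting and are not supported.
- A reader might infer a loss of about 14 points (.63 under the rule against .77). That comes from a model without baseline PHQ-9 and with one predictor correlating 0.5 with the outcome. The planned HLM contains the baseline measure.
- A reader might infer that the rule contradicts the sample size calculation. That section includes two covariates but does not call them fixed or name them, and it sets their correlation with treatment at 0.1. It can be read as an allowance for covariates found imbalanced.
- A reader might infer that every other covariate is barred. The text says significant variables will be entered, not that only those will be, and an analysis plan not shown may name more.

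**Conclusion.** The point holds in a limited form. The article states a selection rule that works on the wrong property, and the rule reaches the primary model. That is a rule fixed badly, not a detail left to a later plan. The 5% entry probability rests only on randomization and an assumed 0.05 screening level. The 23% to 72% range also assumes 5 to 25 independent candidates.

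The efficiency loss is modest: about .74 to .75 against .78 to .84 under assumed correlations of 0.3 to 0.5, and near 1 point if covariates are as weak as the sample size section supposes. A reader might infer a threat to validity through false-positive findings, but the simulated error rates do not show one. The harm is a covariate set that is not known in advance and some precision given up for no gain. The text should be changed, but the primary comparison is not invalid without the change.

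**What to change.** Delete the between-arm significance tests as a step in choosing covariates. Describe baseline characteristics by arm, and do not use p-values to decide the model.

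Name in advance a small set of prognostic covariates that are already collected. Two would be in line with the sample size section; baseline pain intensity or the FIQ-R total are candidates for the PHQ-9 model. Keep each outcome's own baseline as a repeated measure in its HLM and state that it will not also be entered as a covariate, since that would use it twice.

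The cost is analysis-plan wording, with no new data, visits or participants. What is given up is automatic adjustment for a variable outside the named set that happens to be imbalanced. That can go to a sensitivity analysis.

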#### Experimental arm

When entering the study, this group will be receiving UC for fibromyalgia with co-occurring depression (similar to the control group). In addition to this treatment, participants in this arm will start to receive in-group BA. This intervention is based on the Brief Behavioral Activation Treatment for Depression [21–25], whose aims are (1) to increase engagement with activities associated with pleasure or mastery experiences; (2) to decrease engagement with activities that maintain or increase the risk of depression; and (3) and to remove the barriers that limit the access to gratification. The sessions are well structured and described in the manual. The protocol was originally designed to be applied individually with patients diagnosed with major depression. However, we introduced some modifications so that it can be used with patients diagnosed with fibromyalgia. In particular, a rationale about the relationship between pain and depression was added to the first session. During this session the importance of treating depression in patients with fibromyalgia is highlighted and pain experiences are validated. Furthermore, sessions were simplified so that they can be better followed by participants with cognitive symptoms of fibromyalgia, and a treatment outlet with a summary of the main ideas discussed at each session was created. Finally, the manual has been adjusted to be applied in group sessions (five to eight participants). Core aspects of treatment were not altered. The treatment will last for 10 sessions over 2 months. Two psychologists trained in BA will lead the sessions.

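### The primary two-level HLM has no therapy-group term although BA is delivered in groups; if outcomes within BA groups are positively correlated, standard errors are too small and the stated power is optimistic

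*Protocol article*

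**What the plan says.** All of this is in the protocol article.

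- **Delivery** (Experimental arm): "Finally, the manual has been adjusted to be applied in group sessions (five to eight participants"), with 10 sessions over 2 months led by two psychologists.
- **Group formation** (Randomization): women are randomized in batches of about 16, "eight of them being assigned to the experimental arm and the other eight to the control". Batches may be smaller or larger for logistic reasons.
- **Comparator** (Overview of the study design): controls continue usual care alone while the two arms are compared.
- **Analysis** (Data analyses): the HLM for the primary and secondary outcomes is described as follows: "This analysis involves two levels of analysis: within-subject (level 1, which analyzes the change of subjects over time) and between-subject". The treatment effect is examined at the second of these levels.
- **Power** (Sample size calculation): "a sample of 90 participants will be needed to reach a power of .80". The inputs are listed in detail, including "The treatment effect on the slope (standardized Beta) was specified as 0.45". No therapy-group ICC or design effect is among them.
- **Robust standard errors** (Missing data): offered for variables that are not normally distributed, not for group membership.

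**The concern.** Women in one BA group share therapists, peers and ten sessions, so their outcomes may resemble each other more than those of women in other groups. Controls have no such grouping. This is a partially nested design, with clustering in one arm only. The stated model treats all 45 BA women as independent, which is right only if the therapy-group ICC is zero, and the article neither states nor argues that.

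The primary efficacy test is at stake, as is every secondary outcome analysed the same way. If the ICC is positive, confidence intervals are too narrow and the false-positive rate exceeds its nominal level. Power computed without the term then overstates what a valid analysis can deliver. The Discussion also expects the results to support BA in group format, so variation between groups bears directly on the claim to be made.

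**Working it through.** **1. The plan's own figure.** The stated figure is N = 90 for power .80. A linear growth model with the article's inputs was tried in 80 variants, varying the time coding, the scale of the treatment variable, the reading of the slope variance, the residual variance, and whether treatment may affect the intercept. Power ran from 0.23 to above 0.99, and no variant came within 2 points of .80. The article does not fix enough of these inputs to confirm or refute its figure. Below, .80 is taken as given and only the relative loss is computed.

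**2. Inputs.**
- 45 women per arm (article).
- Group size m = 7.5, which lies within the stated five to eight: 45 / 7.5 = 6 groups. Groups of 5 would give 9.
- ICC: not stated, so 0 to 0.10 is assumed.
- Alpha: not stated, so two-sided 5% is assumed.
- No batch effect shared by both arms (assumed, relaxed under the objection).

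**3. Formulas,** on the scale of each woman's change, with equal variance in both arms.
- Design effect in the BA arm: DE = 1 + (m − 1) × ICC.
- Ratio of true to modelled standard error (SE): f = √[(DE + 1)/2], because only one arm is clustered.
- Understatement of the model SE: 1 − 1/f.
- Actual type I error: 2 × [1 − Φ(1.96/f)].
- Large-sample power with a valid SE: Φ(2.80/f − 1.96), where 2.80 = 1.96 + 0.84 corresponds to power .80.
- Satterthwaite degrees of freedom: (DE + 1)² / (DE²/5 + 1/44), from 6 − 1 = 5 between BA groups and 45 − 1 = 44 between controls. Power then comes from the noncentral t distribution with noncentrality 2.80/f.

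Example at ICC 0.05:
- DE = 1 + 6.5 × 0.05 = 1.325, and f = √1.1625 = 1.078.
- 1.96/1.078 = 1.818, so type I error is 6.9%. The SE is understated by 1 − 1/1.078 = 7%.
- Large-sample power is Φ(2.80/1.078 − 1.96) = Φ(0.64) = .74.
- df = 2.325²/(1.325²/5 + 1/44) = 14.5, giving power .68.

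| ICC | DE | f | SE understated | Type I error | Power, large-sample | df | Power, small-sample |
|---|---|---|---|---|---|---|---|
| 0 | 1.000 | 1.000 | 0% | 5.0% | .80 | 18.0 | .75 |
| 0.01 | 1.065 | 1.016 | 2% | 5.4% | .79 | 17.1 | .74 |
| 0.02 | 1.130 | 1.032 | 3% | 5.8% | .78* | 16.3 | .72 |
| 0.05 | 1.325 | 1.078 | 7% | 6.9% | .74 | 14.5 | .68 |
| 0.10 | 1.650 | 1.151 | 13% | 8.9% | .68 | 12.4 | .61 |

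*.775 before rounding.

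**4. Smaller groups.** With nine groups of 5, type I error is 5.2%, 5.5%, 6.2% and 7.4% at ICC 0.01, 0.02, 0.05 and 0.10.

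**5. Simulation.** Two-sample t tests on simulated trials (40,000 per setting) agreed with the formula to within about 0.3 points. Four-wave growth data (20,000 per setting), analysed by maximum likelihood with subject-level robust SEs and a large-sample z test, gave 6.7 to 7.5% at ICC 0.05 and 8.0 to 9.9% at ICC 0.10, against 5.6% at ICC 0. The lower figure is for groups of 5, the higher for mostly 8. Robust SEs at the level of the woman do not remove the excess.

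**The case against.** **The article may only be a condensed account.** That would excuse silence, but the article is not silent: it names the number of levels and what each contains, and the power model matches. This defence does not stand.

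**The error is conditional.** A reader might infer that the type I error of this trial exceeds 5% as a matter of fact. The article does not support that: it gives no ICC and no alpha. At ICC 0 there is no inflation, and at 0.01 it is 0.2 to 0.4 points. The inflation also refers to a null of zero average effect with group effects that vary. If BA did nothing at all, no BA-specific group effect would arise. This stands and limits the claim.

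**Batch randomization partly offsets the problem.** Effects shared by both arms of a batch cancel in the comparison but stay in the two-level model's variance, which makes its SE too large. With a shared-batch ICC b (assumed), the variance ratio is about 1 − b + ICC × (m − 1)/2:
- ICC 0.02, b 0.05: 1 − 0.05 + 0.065 = 1.015, type I error 5.2%.
- ICC 0.02, b 0.10: 0.965, type I error 4.6%.
- ICC 0.05, b 0.05: 1.1125, type I error 6.3%.

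So at small therapy-group ICCs even the direction is not guaranteed. At larger ones the excess remains.

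**Closed groups.** The article does not call the groups closed. That membership stays fixed is a fair inference from batch formation, but it is an inference.

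**The remedy costs more than wording.** With about six groups the group variance is poorly estimated, and small-sample degrees of freedom lower power even at ICC 0 (.75 rather than .80). This stands and belongs in the stated cost.

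**Conclusion.** The concern holds in conditional form. The plan explicitly specifies a primary model, and a power calculation, that omit the grouping created by its own intervention. If BA-specific group correlation is positive beyond any shared batch effect, the treatment-effect SE is understated and the test is liberal: modestly so at ICC 0.01 to 0.02 (5.4 to 5.8%), and more clearly at 0.05 to 0.10 (6.9 to 8.9%). These figures assume two-sided 5%, six groups of 7.5 and no shared batch effect. Smaller groups give somewhat less.

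The power figures are losses relative to the stated .80. A reader might take them as this trial's actual power, or take the failure to reproduce .80 as proof that it is wrong. Neither follows, because the article leaves the time coding and scaling of the power model open.

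Severity: should be fixed. The inflation over the lower part of the plausible range is too small, and too dependent on unstated quantities, to call the primary test invalid.

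**What to change.** 1. Record a therapy-group identifier for every BA woman, and the randomization batch for every woman.
2. In Data analyses, replace the two-level model with a partially nested one: a random therapy-group effect on change for BA women only, each control as her own cluster, and a batch term if needed.
3. Specify small-sample degrees of freedom (Kenward-Roger or Satterthwaite). If Mplus does not provide them for this model, name software that does.
4. In Sample size calculation, state alpha and restate power with the group term over an ICC range that includes 0.
5. Settle this before allocation is unblinded for analysis.

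**Cost.** No new patients or outcome data are needed: the change is analysis wording, two recorded identifiers and a revised power statement. The drawbacks are wider confidence intervals, a group variance estimated imprecisely from six to nine groups, and a clearly lower stated power (about .75 at ICC 0 to .61 at ICC 0.10 with six groups, taking .80 as the starting point).
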